**Abstract**

Vascular calcification (VC) is an active process, resulting from the disturbance of balance between inhibitors and promoters of calcification, in favor of the latter. Matrix Gla Protein, a powerful inhibitor of VC, needs vitamin K to become active. In vitamin K depletion, plasma levels of the inactive form of MGP, dephosphorylated, uncarboxylated MGP (dp-ucMGP) are increased and associated with VC and cardiovascular (CV) outcomes. End Stage Renal Disease (ESRD) patients have increased circulating dp-ucMGP levels and accelerated VC. VItamin K In PEritoneal DIAlysis (VIKIPEDIA) is a prospective, randomized, placebo-controlled trial, evaluating the effect of vitamin K2 supplementation on arterial stiffness and CV events in ESRD patients undergoing peritoneal dialysis (PD). One hundred and twenty PD patients will be included in the study. At baseline, dp-ucMGP and pulse-wave velocity (PWV) will be assessed and then patients will be randomized (1:1 ratio) to vitamin K (1000 μg MK-7/day) or placebo for 1.5 years. The primary endpoint of this trial is the change in PWV in the placebo group as compared to the treatment group and the occurrence of CV events. Secondary endpoints are mortality, changes in PD adequacy, change in 24-hour ambulatory blood pressure indexes and aortic systolic blood pressure and changes in calcium/phosphorus/parathormone metabolism.

VIKIPEDIA is a new trial aiming to determine the effect of vitamin K2 supplementation on VC, CV disease and calcium/phosphorus metabolism, in PD patients. The protocol of this study is registered at ClinicalTrials.gov with identification number NCT04900610.

1. **Introduction**

The heavy cardiovascular (CV) burden seen in these patients might be partially explained by the fact that chronic kidney disease (CKD) is a state of accelerated vascular calcification (VC) of both the media and intima arterial wall. VC of the arterial tunica media leads to arterial stiffness which is progressively increased in parallel to CKD progression to End-Stage Kidney Disease (ESKD). Pulse wave velocity (PWV), a marker of arterial stiffness, is increased in uremia and is closely associated with CV disease (1). Compared to hemodialysis (HD), patients undergoing Peritoneal Dialysis (PD) have higher PWV values and wave reflection indices, suggesting a possible higher CV risk in this population (2). Moreover, although several ongoing randomized controlled trials (RCTs) assess various calcification scores as outcomes, we will chose PWV because calcification scores are thought to reflect the final and less dynamic stage of VC, whereas PWV might be subjective to change through time (3). This is why, PWV has served as a potential therapeutic target to ameliorate CV risk in ESKD patients in several trials (4).

For a long time, VC was considered as a passive, degenerative process of calcium accumulation within the arterial wall. Our perspective changed during the recent decades, when it was discovered that VC is an active process regulated by inhibitors and promoters. Among these, Matrix Gla Protein (MGP) is the most powerful natural inhibitor of VC found in the human body. The pivotal clinical role of MGP was firstly showed in knock-out experimental models (MGP -/-) that died within 8 weeks from birth due to severe aortic calcification which led to blood-vessel rupture (5). To become fully active, MGP needs to undergo vitamin K2-dependent carboxylation and then vitamin K2-dependent phosphorylation. Only then MGP can exert its beneficial protective effects against VC (6). In vitamin K deficiency, high circulating levels of the inactive, dephosphorylated uncarboxylated MGP (dp-ucMGP) are reported in both experimental and clinical studies (7). Both in vivo and in vitro data suggest that compared to vitamin K1, menaquinone-7 (MK-7), a long-chain isoform of K2, has significantly longer half-life, higher bioavailability and bioactivity (8) and thus its supplementation is preferred over K1 in RCTs.

Both VC and vitamin K deficiency are thought to be interrelated entities that are highly prevalent even at early stages of Chronic Kidney Disease (CKD) stages 1+2, are gradually increased along with disease progression to advanced CKD stages 3+4 and are further exacerbated in ESKD (CKD stage 5) (9). In CKD and HD populations, dpuc-MGP has been repeatedly associated with various markers of VC and stiffness, including PWV (10, 11), whereas accumulating evidence suggest a tight association between circulating dp-ucMGP, mortality and CV disease in pre-dialysis CKD (12-14) and ESKD patients undergoing maintenance HD (15) or PD (16). Of note, of all the reported data on dp-ucMGP in CKD populations, only the study by Xu et al., was conducted in PD patients.

In the light of the growing body of data supporting the tight association between vitamin K deficiency and VC in uremia, several investigators are currently conducting randomized clinical trials examining the possible therapeutic effect of MK-7 supplementation on VC in ESKD patients (17) undergoing maintenance HD (BASIK2, VitaVasK, VitaK-CAC, Trevasc-HDK and Aortic Valve DECalcification trials). In *clinicaltrials.gov* the search terms “vitamin K” and “hemodialysis” produces 20 results of ongoing or completed RCTs (assessed 23/02/2021). However, none of these trials have been conducted in PD patients, but only in pre-dialysis CKD and/or HD subjects. Moreover, the majority of these trials assessed surrogate VC markers and not clinical hard end-points such as mortality and CV events and no study so far has evaluated the potential effect of MK-7 intake on 24-h ambulatory blood pressure (BP). Another issue of on-going RCTs in HD patients is that the daily dosage of MK-7 is usually below 500 μg/day (18). The precise required MK-7 dosage to restore vitamin K depletion and thus fully activate MGP in ESKD patients is not yet determined. However, in a dose-finding study in prevalent HD patients, Caluwe et al., showed that a daily dosage of 463 μg MK-7 caused a moderate 46% decrease in dp-ucMGP levels and therefore, it was considered under-therapeutic (19). Moreover, supplementation of MK-7 dosages<463 μg/day in HD patients failed to show any beneficial effect on VC in a recent RCT (20). Under these results, in another ongoing RCT in HD patients the proposed dosage of MK-7 is much higher -2 g thrice weekly (trial number *NCT04539418).* The proposed Vitamin K In PEritonial DIAlysis (VIKIPEDIA) study will assess whether high (1g/day) per os intake of MK-7 can enhance MGP activation, suppress dp-ucMGP and thus improve arterial stiffness and ameliorate CV disease.

Oral administration of vitamin K2 might improve MGP carboxylation and phosphorylation status and thus decrease circulating dp-ucMGP. Vitamin K2 (Menaquinone-7, MK-7) is the first and most clinically approved and validated K2 supplement (MenaQ7 ®, Nattopharma, ASA, Hovik, Norway) with proven efficacy in reducing dp-ucMGP (21) and has been used in several clinical trials in HD patients (19, 22). Vitamin K2 is a natural supplement, that can be purchased over the counter from drug stores or even super markets, without physician’s prescription, because it is not a drug. Millions of people around the world are receiving vitamin K2, because it is thought to have several beneficial effects, whereas not toxicity or side effects have been reported. In the VIKIPEDIA study we will administer orally, daily, high dosage of MK-7 to PD patients. Although several clinical trials have administered MK-7 in dosages 200-500 μg/day, this is the first RCT administering 1g/day in PD patients. There are no safety concerns with this dosage, because other RCTs have administered MK-7 in ESKD, without reporting thrombotic events, side-effects or complaints (22).

Therefore, since ESKD patients undergoing PD present significant reduced K2 levels compared to pre-dialysis CKD patients, we believe that such a high dose is justified in our cohort and the potential beneficial effects of high-dose treatment might outweigh the potential side-effects. Finally, so far, no study has assessed the pharmacokinetics and pharmacodynamics of dp-ucMGP in PD patients and the concentration of dp-ucMGP in the PD effluent, after a PD session. Therefore, the proposed VIKIPEDIA study is novel and timely.

1. **Objectives**

The major outcome of interest of the VIKIPEDIA study is whether oral administration of MK-7 in ESKD patients undergoing PD can slow progression of arterial stiffness. We expect that MK-7 supplementation will enhance MGP carboxylation and phosphorylation, suppress circulating dp-ucMGP, slower progression of arterial stiffness [assessed by PWV increase] and thus ameliorate CV disease. Further research questions will be whether treatment with MK-7 might reduce all-cause and CV mortality and improve 24-hour ambulatory BP. Our research hypothesis is that daily, high dosage of MK-7 supplementation might increase γ-carboxylation and thus activation of MGP, decrease circulating dp-ucMGP and thus ameliorate CV disease in the PD population. Moreover, we will assess cross-sectional information regarding the prevalence of arterial stiffness and vitamin K deficiency in PD patients, along with prospective data on the development of arterial stiffness in PD patients in the control group (not treated with MK-7).

1. **Materials and Methods**

*Trial Design and Setting*

VIKIPEDIA is a multi-centre, placebo-controlled, randomized, open-label intervention clinical trial on PD patients. Our study protocol was developed in accordance with the Helsinki Declaration of Human Rights and the Good Clinical Practice Guidelines and Standard Protocol Items: Recommendations for Intervention Trials (23), was approved by the Ethics Committee/Scientific Council of the Medical School of Aristotle University of Thessaloniki (235/14.05.2021). All participants will provide a structured, written, informed consent. Three university, tertiary hospitals in Northern Greece with major, referral PD units will participate in the study. The design of the trial is presented in figure 1. In short, the patients will be recruited within 1 year. At baseline, all eligible patients who have provided a written, informed consent will be enrolled in the study. Αortic stiffness and vitamin K status will be assessed by PWV and plasma dp-ucMGP levels respectively. Before randomization, we will draw blood (serum and plasma) and PD fluid samples from all patients to measure blood count and routine biochemical parameters, including urea, creatinine, potassium, sodium, calcium, phosphorus, c-reactive protein, alkaline phosphatase, albumin, parathormone, 25-OH D3, magnesium, glycated hemoglobin, thyroid function hormones. Since both vitamin D and magnesium are considered of utmost importance in vitamin K metabolism, after baseline, patients with vitamin D and/or magnesium depletion will be treated with oral supplements to achieve normal levels of both elements, before randomization. Our cohort will then be categorized to one of the two groups (placebo or active group) and the treatment period will last 1.5 years. As mentioned before, vitamin K2 is a natural supplement, that can be purchased over the counter and it is not a drug.

To ensure that the two parallel groups will include patients that will not differ significantly in vitamin K and stiffness we will stratify the patients accordingly. However, since the clinicians that will assess PWV, 24hour BP and the study endpoints will be blinded to the treatment, information bias is excluded. After randomization, all patients will continue their routine, standard medical treatment and patients in the treatment group will additionally receive daily, per os 1 g of vitamin K2 (MenaQ7 ®, Nattopharma, ASA, Hovik, Norway).

*Inclusion and exclusion criteria*

Inclusion and exclusion criteria of this study are shown in Table 1.

*Marker of vitamin K deficiency*

As a marker of vitamin K deficiency we will assess plasma dp-ucMGP at baseline and the end of the study. Additional parameters that will be measured are vitamin K plasma concentration and proteins induced by vitamin K absence-II (PIVKA-II). Blood will be obtained from patients and plasma will be immediately stored at -80°C, until dry ice transfer for analysis in VitaK, Maastricht, the Netherlands, as described before (24).

*Measurement of arterial stiffness*

One of the primary outcomes of the trial is the increase in arterial stiffness, evaluated by PWV.

*Tonometric measurement of arterial stiffness and central aortic BP with the Sphygmocor device*

Radial artery applanation tonometry with the a high-fidelity, pencil-type SPT-301 (Millar Instruments, Houston, TX) probe interfaced with a computer running Sphygmocor software (ArtCor, Sydney, Australia), will be performed to estimate central hemodynamic indices. The Sphygmocor software regenerates the aortic pulse waveform via mathematical transformation of the radial pulse waveform (generalized transfer function). Aortic pulse waveform will be calibrated by inserting the brachial systolic BP (bSBP) and brachial diastolic BP (bDBP) recorded immediately before the Sphygmocor measurement (25). Augmentation pressure (AP) will be defined as the difference of aortic pressures between the second and first systolic peaks. Augmentation index (AIx) will be calculated as the ratio of AP to aortic pulse pressure (PP) and will be expressed as percentage (%). Heart rate-adjusted AIx (AIx(75)) will be estimated by adjusting AIx at an inverse rate of 4.8% for each 10 beats per minute increase in heart rate (2;6). Aortic PWV will be determined by performing applanation tonometry at the carotid and femoral arteries with the above-described pencil-type tonometer (26). Pulse waveforms will be referenced to a concurrently recorded ECG, and pulse wave transit time between the subsequent recording sites will be calculated using the foot-to-foot time difference between carotid/femoral waveforms (27). Body surface distances from the suprasternal notch to the carotid recording site (distance A) and from the suprasternal notch to the femoral recording site (distance B) will be measured and pulse wave travel distance will be calculated by subtracting the distance B from distance A. Aortic PWV will be estimated by dividing the pulse wave travel distance to transit time. We will measure PWV over ten consecutive heartbeats to cover a complete respiratory cycle. The first valid tonometric measurement will be used in statistical analysis (25).

Secondary outcomes will be the changes in ambulatory BP indices.

*ABPM with the Mobil-O-Graph device*

Brachial and central aortic BP, AIx and PWV will be recorded under ambulatory conditions over 24 hours with the brachial cuff-based oscillometric device Mobil-O-Graph (IEM, Stolberg, Germany) (28). The BP-detection unit of this device was validated according to the criteria of European Society of Hypertension/European Society of Cardiology (ESH/ESC). The monitor is programmed to measure BP 3 times per hour during daytime (07:00 to 22:59) and 2 times per hour during nighttime (23:00 to 06:59). ABPM will be considered complete when >80% of readings will be valid with ≤2 non-consecutive daytime hours with <2 valid recordings and ≤1 nighttime hour without valid recording. Participants with incomplete or invalid recordings will be asked to repeat ABPM within the next week.

The methodology incorporated by the Mobil-O-Graph device is described in detail elsewhere (29). After the oscillometric recording of brachial BP, the cuff re-inflates at the diastolic phase, acquiring the brachial pressure waveforms for ~10 seconds with a high-fidelity pressure sensor (MPX5050, Freescale, Tempe, AZ, USA). Subsequently, the software (HMS version 4.5) regenerates the aortic pulse waveform by means of an ARCSolver algorithm using a generalized transfer function. The calculation of central aortic pressures was based on the C1 (brachial systolic BP /diastolic BP) calibration method. The Mobil-O-Graph device performs also wave separation analysis by decomposing the aortic pulse waveform into forward- and backward-traveling pulse waves with a triangular aortic flow waveform (27). Utilizing parameters from pulse wave and wave separation analyses, the ARCSolver algorithm estimates the following indices:

1. augmentation pressure, defined as the difference of the pressure at second minus the pressure at first inflection point of the systolic phase of pulse wave;
2. AIx, an index of pulse wave reflection at the level of microcirculation, defined as the ratio of augmentation pressure to aortic PP;
3. PWV, a direct marker of arterial stiffness, calculated from the reconstructed aortic pulse waveform via mathematical algorithms, taking into account the characteristic impedance and age and assuming a three-element Windkessel model.

*Study endpoints*

We will consider two primary endpoints:

-Progression of aortic stiffness, assessed by the absolute change in the value of PWV after 1.5 years of treatment compared to PWV at baseline before the initiation of treatment.

-The occurrence of non-fatal CV events, including acute myocardial infarction, acute coronary syndrome, embolism, peripheral arterial disease and stroke.

We will consider the following secondary endpoints:

-All-cause and CV mortality

- The absolute change from baseline in the values of PWV indices, wave reflection indices, heart-rate-adjusted augmentation index, SVRI and PP

-The percentage change over time in the values of PWV indices, wave reflection indices, heart-rate-adjusted augmentation index SVRI and PP

-PD adequacy (RRF preservation, Kt/V)

- Rate of infections and peritonitis

-The absolute change in 24 hour ambulatory BP indexes and aortic systolic BP

-Changes in serum parathormone from baseline

-Changes in the calcium phosphorus product from baseline

- Fracture incidence

- Incidence of joint/muscle pain

*Statistical analysis*

All eligible patients who provided informed consent will be enrolled and randomized to the treatment or placebo group (on a 1:1 ratio), stratified by sex, age and center. All details will be described in a statistical randomization report that will be kept concealed and will be opened only after the enrollment will be completed.

One of the primary endpoints is progression of arterial stiffness, defined as the absolute change in PWV value at the end of the 18 months versus the baseline. We hypothesize that the progression – increase of PWV will be lower in the treatment group (20% lower). Therefore, this endpoint will be the PWV increase for every patient (expressed as absolute value and as percentage change over time). To investigate the possible effect of MK-7 supplementation on the other primary endpoint (CV events) Kaplan-Meier curves and Cox regression analysis will be performed.

*Sample size calculation*

We performed two separate power calculations for our two separate, primary endpoints. The only published study so far assessing dp-ucMGP and clinical hard end-points in PD patients, showed that after a median follow-up of 31 months, a significantly higher incidence of fatal/non-fatal CV events occurred in the patients with high dp-ucMGP levels (64.6% versus 39%). Until to-date no RCTs have been conducted in PD patients, therefore our calculation will be based on already published data in similar populations. We consider that a 28% difference in the incidence of CV events among arms is a significant treatment effect and we expect that the incidence of CV events would be 56% in the placebo and 28% in the treatment group, during the 18 month follow-up. Therefore, with a two-sided significance level of 5%, t-test and 80% power, 96 participants will be required. Accounting for a drop-out of 20%, we will enroll 120 patients (60 in each arm).

For the primary outcome of arterial stiffness progression we performed a separate power analysis. Based on previous studies, we expect that the increase in PWV value (absolute difference from baseline to the end of the study) will be 3 m/s after 1.5 year at the placebo group with an assumed standard deviation of 0.90 m/s (3, 30, 31) and we consider that an absolute difference of 20% in PWV increase among groups, is a significant treatment effect (32, 33). Accounting for an estimating drop-out rate of 20%, with a two-sided significance level of 5%, t-test and 80% power, 120 patients will be required (60 in each group) to detect a significant treatment difference.

*Monitoring*

During the study period, 6 follow-up visits will take place, at months 3, 6, 9, 12, 15 and 18 respectively. In all these visits, patients will be interviewed regarding the compliance and potential side effects (and pills will be counted), and clinical examination and routine blood sampling will be performed. To evaluate the patients’ compliance, the drug boxes will be thoroughly checked and remaining pills will be counted and reported. As before enrollment, all patients will undergo standard, regular follow-up visits every month in their PD unit. At the end of the follow-up period, all plasma and serum parameters that were measured at baseline, along with PWV will be re-assessed. The occurrence of the trial’s endpoints will be documented by death certificates, medical files and records and integrated interview at the last visit or telephone interviews. During the study period, all potential adverse events will be closely monitored and recorded. These data will be evaluated thoroughly. The criteria for early termination of the trial will be withdraw of the written consent, death, kidney transplantation, severe allergic response to MK-7 and medical necessity for treatment initiation with vitamin K antagonists.

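### In patients with vitamin D or magnesium depletion, the endpoint baseline is taken before a pre-randomisation repletion period of unstated length, so their change from baseline is not an 18-month change

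*Protocol*

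**What the plan says.** All references are to the Protocol.

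- **Trial Design and Setting** gives the order of events. PWV and dp-ucMGP are assessed at baseline. On bloods it says: "Before randomization, we will draw blood (serum and plasma) and PD fluid samples from all patients to measure blood count and routine biochemical parameters". The list that follows includes calcium, phosphorus, parathormone, 25-OH D3 and magnesium. Next comes: "after baseline, patients with vitamin D and/or magnesium depletion will be treated with oral supplements to achieve normal levels of both elements, before randomization". After that: "Our cohort will then be categorized to one of the two groups (placebo or active group) and the treatment period will last 1.5 years".
- **Study endpoints** defines the PWV primary endpoint as the absolute change after 1.5 years of treatment, "compared to PWV at baseline before the initiation of treatment". The secondary endpoints include "Changes in serum parathormone from baseline" and the corresponding change in the calcium-phosphorus product.
- **Statistical analysis** restates the PWV endpoint as the "absolute change in PWV value at the end of the 18 months versus the baseline".
- **Monitoring** re-assesses PWV and the baseline blood parameters at the end of follow-up. It states no PWV measurement between repletion and randomisation.
- **Objectives** also promises "prospective data on the development of arterial stiffness in PD patients in the control group", and cross-sectional data on the prevalence of stiffness and vitamin K deficiency.
- The **Abstract** leaves the repletion step out: "At baseline, dp-ucMGP and pulse-wave velocity (PWV) will be assessed and then patients will be randomized (1:1 ratio").

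**The concern.** A change-from-baseline endpoint should start at or close to randomisation. Here the clock starts earlier for some patients. Anyone found depleted has the reference PWV taken, is supplemented until levels are normal, and only then enters the 18-month period. The recorded change contains the 18 months, the repletion time, and whatever repletion itself does.

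Three results are exposed:

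- **PWV change.** Intervals differ between patients, which adds variance to a primary endpoint.
- **Parathormone and calcium-phosphorus changes.** Vitamin D repletion plausibly acts on these, so their baseline may not represent the state at the start of study treatment.
- **Control-arm progression.** A longer interval that includes an intervention would be reported as 18-month progression.

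A statistical analysis plan can choose among measured values, but it cannot supply a pre-randomisation PWV that the visit schedule never collected.

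**Working it through.** **1. Sequence.** From Trial Design and Setting: baseline measurements, then repletion (depleted patients only), then randomisation, then 18 months. The timing of PWV is explicit. That parathormone, calcium and phosphorus are drawn before repletion is an inference: the text says only that the draw precedes randomisation, but the same list contains the 25-OH D3 and magnesium results needed to detect depletion.

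**2. Inputs from Sample size calculation.** Placebo increase 3 m/s over 1.5 years; SD 0.90 m/s; effect 20% of 3 = 0.6 m/s; two-sided 5%; 60 per arm; 20% dropout, so 60 × 0.8 = 48 completers per arm.

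**3. The plan's own figure.** With difference 0.6 and SD 0.90, 80% power needs 36 per arm by the normal approximation: 72 in total, and 72/0.8 = 90 after dropout, not 120. At 90% power the result is 48 per arm, 96 in total, and 96/0.8 = 120. So the stated 120 corresponds to 90% power, not 80%. That mismatch is a separate matter, but it explains why the reference power below is about 0.90. The exact two-sample t-test with 48 per arm gives 0.898.

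**4. Assumptions the document does not supply.** A share *f* of patients is depleted, and each needs *L* months. PWV rises linearly, repletion has no effect of its own on PWV, and depletion is unrelated to the rate of progression.

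**5. Formulas.**

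- Monthly rise: 3/18 = 0.167 m/s.
- Added to a depleted patient's change: 0.167 × *L*.
- Added to the arm mean: *f* × 0.167 × *L*.
- SD of change: √(0.81 + *f*(1 − *f*)(0.167 × *L*)²).

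Example with *f* = 0.5, *L* = 3: the added variance is 0.25 × 0.5² = 0.0625, so SD = √0.8725 = 0.934. The added mean is 0.5 × 0.5 = 0.25 m/s.

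**6. Results** (exact t-test, 48 per arm, difference 0.6 m/s, *f* from 0.25 to 0.75):

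| *L* (months) | Added per depleted patient (m/s) | Added to arm mean at *f* = 0.5 (m/s) | SD of change | Power |
| --- | --- | --- | --- | --- |
| 0 | 0 | 0 | 0.90 | 0.898 |
| 1 | 0.17 | 0.08 | 0.90 | about 0.90 |
| 2 | 0.33 | 0.17 | 0.91–0.92 | 0.89 |
| 3 | 0.50 | 0.25 | 0.93 | 0.88 |
| 6 | 1.00 | 0.50 | 1.00–1.03 | 0.81–0.83 |

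**7. Relative effect.** At *f* = 0.5, a true 0.6 m/s difference becomes 0.6/3.25 = 18.5% of the observed placebo change (*L* = 3) or 0.6/3.5 = 17.1% (*L* = 6), instead of 20%.

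No such calculation is possible for parathormone or the calcium-phosphorus product, because the document gives no figure for how they respond to repletion.

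**The case against.** The strongest reply is that nothing in the randomised comparison is biased. Repletion precedes randomisation and applies to both arms alike, so its effect and the extra time cancel in expectation. That stands. For the same reason, the 0.17 m/s per month should not be read against the 0.6 m/s target as if it were an error in the treatment effect.

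The power loss rests on an assumed share and duration. It is negligible for 1 to 2 months, and even the worst case shown stays above the 80% that the protocol asks for. That also stands.

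The design flow-chart (Figure 1) is not available in the text and may show visit timing. This tempers the statement that the repletion length is unspecified, but the written text sets no limit.

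The protocol's link between vitamin D, magnesium and outcome concerns vitamin K metabolism. It does not say that parathormone or calcium-phosphorus will move, so that effect is possible, not demonstrated.

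An early measurement also has a use: it serves the cross-sectional prevalence aim. Trial Design and Setting further says that patients will be stratified on vitamin K status and stiffness, and dp-ucMGP is shipped frozen to an external laboratory, so it must be drawn before the day of randomisation. (Statistical analysis names sex, age and center instead; the two passages need reconciling.) Any fix has to respect this.

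A reader might infer that every change from baseline is affected, or that within-arm changes cannot be interpreted at all. The documents do not support either reading. Only depleted patients are supplemented, and a 0.25 m/s excess on 3 m/s is about 8%.

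**Conclusion.** The point holds for depleted patients. Their baseline PWV, and by natural inference their parathormone, calcium and phosphorus, precede a repletion period with no stated end, and no later pre-randomisation value is planned. Their change from baseline is therefore longer than the 18 months in the endpoint definition and includes an intervention.

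The between-arm estimate is not biased in expectation. The consequences are modest loss of precision on PWV (little up to 2 months; power about 0.88 at 3 months and 0.81 to 0.83 at 6), a possible repletion component of unknown size in two secondary endpoints, and a control-arm progression figure that is too high, by about 0.25 m/s if half the patients need 3 months. All sizes depend on the assumed share, duration and linear progression. The change is worth making because it is cheap and a missed pre-randomisation measurement cannot be recovered afterwards.

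**What to change.** **Preferred.**

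- Keep the enrolment draw (25-OH D3, magnesium, dp-ucMGP) for detecting depletion, for stratification and for the prevalence of vitamin K deficiency.
- Take the endpoint baseline PWV, parathormone, calcium and phosphorus after the repletion already planned, at the randomisation visit. The bloods can go on the draw that confirms normal levels.
- In Study endpoints and Statistical analysis, define baseline as the last value before randomisation.
- State the timing of the baseline ambulatory BP recording, which the text leaves open, and add the repletion step to the Abstract.

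**If the order cannot change.** Record depletion status and the baseline-to-randomisation interval, adjust the change analyses for both, and report control-arm progression per unit of actual elapsed time. This handles elapsed time but cannot fully separate a repletion effect on parathormone or calcium-phosphorus.

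**Cost.** A few sentences of protocol text and a reordered visit. PWV is still measured twice per patient, and repletion to normal levels already implies a repeat blood test. The downside is that, in depleted patients, enrolment bloods and baseline PWV are separated in time and stiffness prevalence is measured after repletion.

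### The protocol names two stratification schemes with no factor in common, so the randomisation scheme, and the covariates for the PWV primary that should follow from it, are not fixed

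*Protocol*

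**What the plan says.** Two sections of the protocol describe the stratification.

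- **Trial Design and Setting** gives the aim of arms that "will not differ significantly in vitamin K and stiffness we will stratify the patients accordingly". The same section ties stiffness and vitamin K to measurements: "vitamin K status will be assessed by PWV and plasma dp-ucMGP levels respectively".
- **Statistical analysis** says patients are "randomized to the treatment or placebo group (on a 1:1 ratio), stratified by sex, age and center". It leaves the details to a randomisation report that stays concealed until enrolment is complete.

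Neither section refers to the other, and neither gives a cut-off for age, dp-ucMGP or PWV.

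On the dp-ucMGP assay, **Marker of vitamin K deficiency** says "plasma will be immediately stored at -80°C, until dry ice transfer for analysis in VitaK, Maastricht, the Netherlands". The sites are in Greece: "Three university, tertiary hospitals in Northern Greece with major, referral PD units will participate in the study". No turnaround time is stated.

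On the PWV primary, **Study endpoints** defines it as the absolute change from baseline to 1.5 years and lists percentage change in PWV indices as secondary. **Statistical analysis** says of the primary that "this endpoint will be the PWV increase for every patient (expressed as absolute value and as percentage change over time"). A t-test is named only under **Sample size calculation**. Kaplan-Meier and Cox methods are named for cardiovascular events, and no test or model is named for PWV.

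**The concern.** Whoever builds the allocation list cannot tell from the protocol which factors to use. The choice has consequences.

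- Under sex, age and centre, the design does nothing directly to balance baseline PWV or dp-ucMGP, although the protocol tells the reader that balance on both is ensured. Baseline PWV is half of the primary endpoint.
- Under vitamin K status and stiffness, an assay result from abroad must be in hand before each patient is randomised, and nothing in the protocol shows that it would be.
- Under all five factors as simple strata, the cells become too small for blocking to work.

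The analysis should follow the randomisation. With the factors undetermined, so are the covariates. The sizing implies a plain comparison of changes, which makes no use of the factors and less than full use of the baseline PWV that every patient contributes.

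**Working it through.** **The plan's own sample size.**

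- Cardiovascular events, 56% versus 28%, two-sided 5%, 80% power: 48 per arm, 96 evaluable, 96/0.80 = 120 enrolled. This reproduces the stated figure.
- PWV: placebo increase 3 m/s, 20% difference, so 0.20 × 3 = 0.6 m/s; SD 0.90 m/s. The result is 36 per arm (normal) or 37 (t-test), so 72 to 74 evaluable and 90 to 93 enrolled. The stated 120 for PWV corresponds to about 90% power, not 80%. This matters here only because it shows no shortage of patients for PWV.

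**The two lists side by side.** Trial Design and Setting: dp-ucMGP, PWV. Statistical analysis: sex, age, centre. No factor is common to both.

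**Cell counts.** The three centres come from the protocol. Two levels for every other factor is an assumption, as no cut-offs are given.

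- Sex × age × centre: 2 × 2 × 3 = 12 cells; 120/12 = 10 patients each.
- Adding PWV: 12 × 2 = 24 cells; 120/24 = 5 each.
- Adding PWV and dp-ucMGP: 12 × 2 × 2 = 48 cells; 120/48 = 2.5 each, with two arms to fill.

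**Chance imbalance on a factor not used.** The difference in baseline means, in SD units, has standard error √(2/n) for n per arm. With n = 60 this is √(2/60) = 0.183.

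- Above 0.2 SD: 0.2/0.183 = 1.10, two-sided probability about 27%.
- Above 0.25 SD: 0.25/0.183 = 1.37, about 17%.
- Above 0.5 SD: 0.5/0.183 = 2.74, about 0.6%.

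These figures ignore any correlation of the factor with sex, age or centre, which would lower them.

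**Gain from adjusting for baseline PWV.** With equal variances σ² at baseline and month 18 and correlation ρ:

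- variance of a change score: 2σ²(1 − ρ)
- residual variance under ANCOVA: σ²(1 − ρ²)
- ratio: (1 + ρ)/2

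The correlation is not in the protocol, so a range is assumed. The SD of change is held at 0.90 m/s and power is by the normal approximation.

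| Assumed ρ | Variance ratio | Needed per arm (80% power) | Enrolled after 20% drop-out | Power at 48 per arm |
|---|---|---|---|---|
| change score | 1.00 | 36 | 90 | 90.4% |
| 0.8 | 0.90 | 32 | 80 | 93.1% |
| 0.6 | 0.80 | 29 | 73 | 95.5% |

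Adjustment lowers the requirement; it never raises it here.

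**The case against.** The best defence is that the lists differ but do not exclude each other, and that the randomisation report may settle the matter. The first half stands. A reader might infer that only one scheme can be carried out. That does not follow, because minimisation can handle five factors in 120 patients. What remains is that the protocol nowhere says the lists are to be combined, and a concealed report does not reconcile two statements in the governing document.

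A reader might also infer that dp-ucMGP cannot be known at randomisation. The protocol does not say so. It gives no turnaround time, and there is an interval before randomisation in which vitamin D or magnesium depletion is corrected. That interval is described only for depleted patients, so it does not guarantee time for everyone. Timely availability is not shown, and no more can be said. PWV does not depend on the shipped assay.

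On the analysis, the protocol does not commit itself to an unadjusted comparison of PWV. The t-test belongs to the sizing, a change endpoint is compatible with ANCOVA, and covariates may be in a statistical analysis plan that is not shown. This objection stands. The ANCOVA is therefore the remedy that goes with settling the scheme, not a second error.

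**Conclusion.** The contradiction over the stratification factors is real and should be corrected, ideally before the allocation list is generated. The harm is limited to an unsupported claim of balance and some loss of precision. If only sex, age and centre are used, a difference above 0.2 SD in baseline PWV or dp-ucMGP has a probability of about 27% for each. That is worth guarding against, but a large imbalance is rare. The 48-cell figure rests on the assumed two levels per factor and on simple crossed strata. The 10% to 20% variance reduction rests on equal variances and an assumed correlation of 0.8 to 0.6.

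Two stronger conclusions are not supported. The first is bias: under randomisation an unadjusted comparison of changes is unbiased on average, and ignoring stratification factors generally makes standard errors too large, not too small. The second is a loss of the stated power: on the protocol's PWV inputs, 48 evaluable per arm already gives about 90%.

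A smaller ambiguity belongs with this point. Percentage change in PWV appears both within the primary (Statistical analysis) and among the secondary endpoints (Study endpoints).

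**What to change.** 1. State one randomisation scheme, with cut-offs, in identical words under Trial Design and Setting and under Statistical analysis. Sex, age group and centre is the readily workable option. If balance on stiffness is wanted, add PWV or use minimisation. Use dp-ucMGP only if results can be shown to arrive before randomisation.
2. Remove the balance claim in Trial Design and Setting for any factor not used.
3. Analyse the PWV primary (absolute change or month-18 value; with baseline as a covariate both give the same treatment estimate) by ANCOVA with baseline PWV and the randomisation factors as covariates. Adjustment for log dp-ucMGP is optional.
4. Account for the same factors in the Cox model for cardiovascular events.
5. Keep percentage change in PWV as a secondary endpoint only.

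The cost is wording in the protocol and analysis plan, provided the scheme chosen is the one actually implemented. All the covariates are already collected at baseline, and no more patients are needed. If an allocation list already exists, the text and the analysis should follow the factors it used.
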